**Fig. 1 Fig1:**
[figure not shown]
SPSRS intervention

**Fig. 2 Fig2:**
[figure not shown]
Protocols for the SPSRS intervention

#### Control group

The participants in the Control group will receive a total of at least 50 min of intervention per week, with 10 min of video viewing once per day, five times per week, for a total of at least 50 min per week, after accessing the YouTube website using a researcher-controlled iPad to search for videos of interest to them. If there is no video that the participant wants to watch, the researcher will suggest a video and watch it with the participant’s approval, as described for the Experimental group. The Control group videos will not show confidence-boosting or positive words; the Control group will use the same iPad as did the Experimental group.

### Criteria for discontinuing or modifying the allocated interventions

The research team will discontinue the intervention if any of the following conditions are met by the research subject:

If the research subject wishes to discontinue participation in the research.If the research team determines that it is difficult to continue the study because of deterioration of the mental or physical health of the patient.If the entire clinical study is terminated.If it is discovered after enrollment that a participant does not meet eligibility.If the study team determines that the intervention should be discontinued for any reason.

The date and reason for discontinuation will be fully documented in the case report form. Case reports will provide information on the feasibility and acceptability of the intervention, to improve the standard practice of SPSRS interventions for future full-scale trials. The participants will not be considered to have dropped out of the study upon discontinuation of the intervention; rather, they will be asked to undergo primary and secondary outcome assessments. If a participant refuses to undergo the evaluation or withdraws consent, the participant will be considered as having dropped out of the study. Participants will be excluded from the intention-to-treat (ITT) analysis only if they are found to be unable to meet the eligibility criteria.

### Relevant concomitant care and interventions permitted or prohibited during the trial

This study will not prohibit other forms of care, from an ethical standpoint.

### Outcomes

The primary outcome will be the change in the scores on the Japanese version of the BDI-II at 1 week after the baseline assessment [75]. In turn, the secondary outcomes will be the changes in the minimum amount of exercise at which heart failure symptoms appear on the Specific Activity Scale (SAS) [76], New York Heart Association functional classification (NYHA classification) [77], as well as grip strength at 1 week after the baseline assessment.

### Recruitment timeline

The study will be conducted at the Fujioka General Hospital in Gunma, Japan, from October 2023 to March 2027. The researcher will distribute a brochure with a brief description of the study to potential participants, to encourage their participation. Potential participants will be assessed for eligibility through interviews and questionnaires, and enrolled in the study after baseline assessments (BDI-II and SAS, NYHA classification, and grip strength assessment). The baseline and eligibility assessments will be performed by the researcher within 1 week of admission to the acute wards. The participants will be randomly assigned to the Experimental or Control group after the eligibility and baseline assessments. Both groups will then receive a 10-min video-viewing intervention once per day, five times per week for 1 week. The participants will undergo remeasurements for second BDI-II and SAS, NYHA classification, and grip strength at 1 week after the intervention. A flowchart of the study design is shown in Fig. 3 [78]. The assessment schedule is provided in Table 1 [79].

**Fig. 3 Fig3:**
[figure not shown]
CONSORT flowchart of the study design

**Table 1 Tab1:** Assessment schedule

			**STUDY PERIOD**		
	**Enrolment**	**Allocation**	**Baseline**	**Intervention**	
**TIMEPOINT****	***–1 week***	**0**	***0***	***1 day***	***7 days***
**Enrolment**					
**Eligibility screen**	X				
**Informed consent**	X				
**Allocation**		X			
**Interventions:**					
***Experimental group***					
***Control group***					
**Assessments:**					
***Demographics***	X				
***BDI-II***			X		X
***SAS***			X		X
***NYHA classification***			X		X
**Grip strength**			X		X

* BDI-II* Beck Depression Inventory-II

*SAS* Specific Activity Scale

*NYHA classification* New York Heart Association classification

### Sample size

There are no data on SPSRS interventions for patients with cardiac disease and StD admitted to acute wards, which hampers the estimation of the sample size based on actual data. Although a formal sample size calculation is not required in a pilot study [68], a sample size of 15–20 persons should be maintained in a pilot study for conducting a subsequent full-scale study [80]. Therefore, the goal of this study was to recruit 15 participants per group, for a total of 30 participants.

### Allocation

The participants will be randomly assigned to the Experimental or Control group in a 1:1 ratio after the eligibility criteria check and baseline assessment. Using a computer (Excel software), a randomized list will be generated using the permuted block method. To ensure allocation concealment, the block sizes will not be disclosed until after trial completion. The generation of the randomized list will be performed by a third party not involved in the study. Throughout this process, the participants, evaluators, and intervention implementers will be denied access to information that might reveal the assignments. The randomized list will be provided to the Central Registration Center located at Gunma University, for random assignment.

### Blinding

It will be difficult to blind the study participants and intervention providers because the Experimental and Control group interventions are distinctly different. In addition, the small number of research staff who will participate in this study renders it difficult to maintain rater blinding. Therefore, this study is planned as an open-label trial.

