## Materials and methods

### Trial design and study setting

The study was designed as a single-center, open-label, pilot, randomized, parallel-group trial. The participants in this study will be older patients with cardiac disease and StD who are admitted to acute wards. We will compare the effects of a video-viewing intervention using the SPSRS (with positive word stimulation) and a video-viewing intervention using YouTube (without positive word stimulation). The Fujioka General Hospital is a public hospital that specializes in the treatment and rehabilitation of disuse syndrome, musculoskeletal disorders, cerebrovascular disorders, respiratory disorders, cardiovascular disorders, cancer, and pediatric disorders. The acute wards of the Fujioka General Hospital provide individual therapy performed by physical therapists (PTs), occupational therapists (OTs), and speech therapists (STs) to promote activities of daily living and independence to leave home among these patients. The acute wards at the Fujioka General Hospital provide individual therapy delivered by PTs, OTs, and STs for a maximum of 6–9 units per day (1 unit = 20 min), 7 days per week, 365 days per year. All patients admitted to these acute wards will be assigned a specific PT, OT, or ST. An alternate PT, OT, or ST may provide rehabilitation services when the assigned PT, OT, or ST is absent or unable to intervene. To prevent biases associated with the study design, this protocol followed the Standard Protocol Items: Recommendations for Interventional Trials (SPIRIT) 2013 statement [69].

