### Interventions

#### Experimental group

The Experimental group will receive a video-viewing intervention using SPSRS. The SPSRS tool is designed to present confidence-boosting words in the video for 17 ms, followed by 150 ms of positive words (Fig. 1). The confidence-boosting words are “can,” “let us try,” “good luck,” “able,” and “do not worry,” which appear randomly in the four corners of the screen [73]. The positive words are “nice,” “great,” “fantastic,” “satisfactory,” and “enjoyable,” and appear randomly in the center of the screen [74]. These words are presented repeatedly every 5 s. An iPad will be used as the medium for video viewing, which will be conducted with the researcher in attendance. SPSRS is used according to the operating manual. After accessing the SPSRS website using a researcher-controlled iPad, the participants will search for videos of interest and watch a 10-min video in the presence of the researcher (Fig. 2). If there is no video that the participant wants to watch, the researcher will suggest a video and watch it with the participant’s approval. The participants will watch the 10-min videos once per day, five times per week for a total intervention time of at least 50 min. The video-viewing time in this study was determined based on a previous study that examined the effects of the SPSRS intervention on patients with StD [64].

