#### Beck Depression Inventory-II (BDI-II)

The BDI-II is a 21-item self-administered questionnaire that measures the severity of depression symptoms. Items are rated using a 4-point Likert scale ranging from 0 to 3 points [84]. The total score ranges from 0 to 63 points, with higher scores indicating more depressive symptoms. The reliability and validity of the BDI-II have been reported in previous studies [75, 84, 85]. This study used BDI-II to identify the presence of StD in older patients with cardiac disease and to measure changes in depressive symptoms during a 1-week intervention. This is because BDI-II, in addition to being widely used to identify StD, is also widely used to assess depressive symptoms in clinical populations, including patients with cardiac disease [65, 70, 86–89].

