### Data management, confidentiality, and access

To ensure data accuracy, the participants’ data will first be transcribed onto paper. Two independent researchers will then enter the data into an Excel spreadsheet. These data entries will be performed on a computer that is not connected to the Internet. All information entered will be stored on a password-protected USB stick. The next step will be the checking of the collected data by researchers other than the two researchers who entered the data for accuracy, missing data, and data consistency [94]. The paper data created previously will be stored in a lockable storage facility at Gunma University, and the electronic data will be stored in a separate lockable cabinet. Backups of electronic data will be created on hard drives that are not connected to the Internet. The participants’ data will be anonymized and managed using random codes. These data will be stored for 10 years after the publication of the article and will be properly erased after the storage period. Only the principal investigator and data manager will have access to the collected data. The principal investigator and data manager will investigate data issues and prepare the dataset for statistical analysis. After publication, only the principal investigator and selected groups of individuals will have access to the dataset. No computer at Gunma University that is connected to the Internet will be used for statistical analysis.

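### Staff numbers do not justify leaving collection and scoring of the self-completed BDI-II open to the researcher who attended the sessions

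*Protocol article*

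**What the plan says.** The Blinding section gives two separate reasons for an open-label trial. For participants and providers it is the nature of the interventions: "It will be difficult to blind the study participants and intervention providers because the Experimental and Control group interventions are distinctly different". For raters it is staffing alone: "the small number of research staff who will participate in this study renders it difficult to maintain rater blinding".

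On the primary outcome, the BDI-II section says: "The BDI-II is a 21-item self-administered questionnaire that measures the severity of depression symptoms".

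On contact with the patient, the Experimental group section says of the viewing: "An iPad will be used as the medium for video viewing, which will be conducted with the researcher in attendance". The Recruitment timeline has the researcher do the baseline and eligibility assessments, before randomization. It does not say who does the 1-week assessment.

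On data handling, the section on data management, confidentiality and access first has the data transcribed onto paper, by whom is not said. Then: "Two independent researchers will then enter the data into an Excel spreadsheet". Other researchers check the entries, and random codes are used. Finally: "The principal investigator and data manager will investigate data issues and prepare the dataset for statistical analysis". The section does not say whether any of these people know the allocation.

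The limitations paragraph of the Discussion concedes that the open label may bias providers, participants and evaluators.

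**The concern.** The staffing reason is applied to all outcomes alike, but the outcomes differ in what they need from staff. A self-completed questionnaire needs nobody to rate it. It needs only someone to hand it over, take it back and add it up, and the article already has people in separate data roles who could do the adding up.

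Nothing in the article keeps the session researcher away from the 1-week BDI-II. A patient who answers mood questions in front of the person who ran the sessions may shade the answers, and that person may help with or interpret items. The Background says that the research team developed the tool. If such influence differs between arms, it enters the primary comparison directly, and the Abstract says that the results will feed into planning a full-scale trial. SAS (asked question by question), NYHA (graded from reported symptoms) and grip (dependent on effort) are also open to an assessor's expectation or encouragement.

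**Working it through.** The plan states no figure on this point, so there is none to reproduce. Two checks apply.

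**1. Does the staffing reason fit the rest of the article?**

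- Data entry: 2 researchers.
- Checking: researchers other than those two, so at least 1 more (the plural suggests 2 or more). Total for entry and checking: at least 2 + 1 = 3.
- A principal investigator and a data manager are also named. They may overlap with the three, so they are not added.
- Work needed to mask BDI-II scoring: adding up 21 items, each 0 to 3, from a sealed form. This is desk work and can be done wherever the data staff sit.
- Work needed to mask NYHA, SAS and grip: a person at the bedside. The article does not show that the data staff are at the hospital.

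So the staffing reason fails for BDI-II scoring and is weak for BDI-II collection. For the three secondary outcomes it may be sound.

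Double entry and independent checking protect against keying errors. They do not protect against anything that happens while the form is being answered or copied onto paper.

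**2. What could a differential bias do at this sample size?** (Illustration only; the document gives no bias size.)

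Inputs: 15 per arm and two-sided 0.05 (Sample size; Statistical methods). Assumptions: no true effect, no dropout, a two-sample t-test with 28 df standing in for the planned mixed model, and a bias *b* in SD units of the outcome compared.

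- Standard error: sqrt(1/15 + 1/15) = sqrt(2/15) = 0.365 SD.
- Noncentrality: *b* / 0.365.
- Rejection rate: the probability that a noncentral t with 28 df lies outside ±2.048.

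| Assumed bias *b* (SD) | *b* / SE | Two-sided rejection |
|---|---|---|
| 0 | 0 | 5.0% |
| 0.1 | 0.27 | 5.8% |
| 0.2 | 0.55 | 8.3% |
| 0.3 | 0.82 | 12.5% |

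Only a difference in bias between arms counts here. Influence that is equal in both arms cancels.

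**The case against.** The strongest reply has five parts.

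- **The weakness is disclosed.** The Blinding section and the limitations paragraph both say that evaluators may be biased. This stands: nothing is hidden. But disclosure does not replace a cheap safeguard, and the limitations paragraph attributes the open label to the nature of the study, which does not explain unmasked raters.
- **For a self-completed scale the patient is the rater, and the patient is not blinded.** This stands in full. A reader might infer that private completion and masked scoring would make the primary outcome unbiased. They would not: patient expectation is probably the larger route and remains. Summing fixed items also leaves a scorer little discretion, so most of the gain on the BDI-II comes from keeping the session researcher away while it is answered.
- **The control is active.** Both arms watch self-chosen videos on the same iPad and schedule, with the same help in choosing, so researcher contact looks similar. This stands: much of any demand effect should be shared, and only the remainder biases the contrast.
- **Spare staff are not proven.** A reader might infer from the count of data researchers, or from "All patients admitted to these acute wards will be assigned a specific PT, OT, or ST", that a masked bedside assessor is already available. The article does not say that data staff are on site or free, and a treating therapist could easily learn the arm from the patient. Masked assessment of NYHA, SAS and grip may therefore need extra staff.
- **Data cleaning.** A reader might infer that cleaning is done with the arm visible. The article does not say so. It is silent, and a full protocol or data-management document may cover it. Coding the arms is a precaution worth stating, not the correction of a known error.

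**Conclusion.** The point holds in a limited form. The only reason given for unmasked raters is staff numbers, and that reason does not cover the primary outcome: the form is self-completed, and researchers with separate data roles are already in the plan. The article permits the session researcher to collect and score the 1-week BDI-II; it does not state that this will happen. Baseline scores are not at issue, because they are taken before allocation.

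The likely gain is modest and cannot be quantified from the document. The range of 5.8% to 12.5% rejection rests wholly on assumed differential biases of 0.1 to 0.3 SD, and part of any such bias would be patient expectation that the change leaves untouched. The documents do not support the wider claims that all rater blinding was avoidable with present staff, or that data cleaning is unmasked. Even so, the safeguards cost little, and they close routes of influence on the primary outcome that the open label does not require.

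**What to change.** 1. **BDI-II at 1 week.** Have the participant complete it privately, without the session researcher, check it for skipped items, and seal it. If help is needed, it should come from someone who did not attend that patient's sessions. The sealed form goes straight to the two data-entry researchers, who score it without the allocation, so that no one who attended the sessions copies or totals it first.
2. **Dataset.** State whether entry, checking and cleaning staff are masked. Keep arms coded A/B until the dataset is checked and locked. The registration center that already holds the randomization list could keep the key.
3. **NYHA, SAS and grip.** Where existing staffing allows, have them taken by a team member who did not attend that patient's sessions. Otherwise leave them as they are and keep the limitation in the Discussion.
4. **Wording.** In the Blinding section, confine the staffing reason to the staff-assessed outcomes, and say that patient expectation on the BDI-II remains.

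Cost: a few lines of procedure, envelopes, and minor scheduling and handling work. Once a form is sealed, missing items can no longer be queried on the spot, hence the check before sealing. Items 1 and 2 use roles already named; item 3 could need more staff, so it is conditional. Sample size, outcomes and analysis model do not change.

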### Data collection

Standard operating procedures and evaluation guides for data collection and storage will be provided to the Fujioka General Hospital, and a 2-h training session will be offered. Meetings will also be held regularly to discuss issues related to the implementation of the trial. The assessments of the primary and secondary outcomes will be conducted according to the schedule provided in Table 1. Age, gender, primary disease at admission, MMSE-J score [81], left ventricle ejection fraction, and blood laboratory data (albumin, hemoglobin, creatinine, and brain natriuretic peptide levels) will be collected as the baseline assessment. In addition, the types of videos viewed by both groups were collected.

#### Mini-mental State Examination (MMSE-J)

The MMSE-J consists of 10 items that assess orientation, registration, attention or calculation, recall, naming, repetition, comprehension, reading, writing, and construction, respectively [81]. Lower MMSE-J scores indicate a more severe cognitive impairment, with total scores ranging from 0 to 30 points. MMSE-J is a reliable and validated assessment that is widely used clinically [82].

#### Mini-international Neuropsychiatric Interview (M.I.N.I.)

The M.I.N.I. is a structured diagnostic interview based on the DSM-IV and ICD-10. The Japanese version of M.I.N.I. is designed to encompass 16 psychiatric diagnostic modules. Respondents can answer “Yes” or “No” exclusively. The reliability and validity of the M.I.N.I. have been reported in previous studies [71, 83].

#### Beck Depression Inventory-II (BDI-II)

The BDI-II is a 21-item self-administered questionnaire that measures the severity of depression symptoms. Items are rated using a 4-point Likert scale ranging from 0 to 3 points [84]. The total score ranges from 0 to 63 points, with higher scores indicating more depressive symptoms. The reliability and validity of the BDI-II have been reported in previous studies [75, 84, 85]. This study used BDI-II to identify the presence of StD in older patients with cardiac disease and to measure changes in depressive symptoms during a 1-week intervention. This is because BDI-II, in addition to being widely used to identify StD, is also widely used to assess depressive symptoms in clinical populations, including patients with cardiac disease [65, 70, 86–89].

#### Specific Activity Scale (SAS)

The SAS lists specific activities of daily living for which exercise intensity (metabolic equivalents: Mets) is mostly known in advance, and participants are asked to answer “Yes,” “No,” or “unknown” in order of the activity with the lowest physical activity index. If the patient answers “Yes,” the question gradually shifts to higher activity, and the point at which the patient answers “No” is the point of the minimum amount of exercise (Met) at which heart failure symptoms appear is calculated [76]. The validity and reliability of the SAS have been reported in previous studies [90].

#### New York Heart Association functional classification

The NYHA cardiac function classification was developed by the New York Heart Association to classify the severity of cardiac disease according to the degree of subjective symptoms observed after physical activity and is widely used as a severity classification in the context of heart failure [77]. This classification includes grade I (presence of cardiac disease but no limitation of physical activity), grade II (mild to moderate limitation of physical activity on exertion, asymptomatic at rest), grade III (severe limitation of physical activity on exertion, asymptomatic at rest), and grade IV (cardiac disease that limits any physical activity and presence of heart failure symptoms and anginal pain even at rest) (77).

